**Sample size calculation**

The adequate sample size for all objectives is calculated using openepi version 3 software. The sample size needed to estimate the utilization of MHS is calculated assuming the anticipated utilization of ANC (74%), births attended in an HF (48%), and PNC (34%) according to the report of 2019 Mini EDHS[[29](#_ENREF_29)], the margin of error of 5%, 95% confidence interval, 1.31 design effect. Based on the above information, the estimated sample size is 392 (ANC), 508 (births attended in a health facility), and 457 (PNC). The sample size needed for identifying the predictors associated with MHSU is calculated considering variables significantly associated with MHSU based on previous studies done in Northern Ethiopia [7], in rural Haramaya district, Eastern Ethiopia [10], and in Northwest Ethiopia [11]. For all calculations, power was set at 80%, level of confidence at 5%, and the ratio of unexposed-to-exposed were assumed to be 1. Hence, the sample size of 1,104 obtained from the second objective will be utilized due to it is the maximum sample size assessed and would be adequate to assess all objectives of this study. The minimum required sample size for the qualitative study will be determined according to the recommendation of Morse and Creswell for Phenomenological studies (20 in-depth interviews, 9 focus group discussions, and 20 key informant interviews) [[30](#_ENREF_30)]. The minimum required sample size for the third and fourth objectives is calculated based on the following considerations. Due to the lack of the previous cRCT on the same topic, assumptions on the proportion of women with knowledge on ODS in the control and intervention arms were taken from a previous quasi-experimental study. The proportion before the intervention was taken as the proportion in the control arm and the proportion after the intervention as the proportion in the intervention arm. Accordingly, P1 = 45.7% (proportion of women’s knowledge regarding ODS during pregnancy) in the control group, P2= 62.9% (proportion of women’s knowledge regarding ODS during pregnancy in the intervention arm) [[14](#_ENREF_14)], 95% CI, and 80% power. According to the above considerations, the estimated effective sample size for individual-based randomization is 286. For this objective, the sample size is adjusted to non-response rate (NRR) by dividing the initial sample size by the anticipated response rate. In case of knowledge regarding ODS during pregnancy, the adjusted sample size to NRR is 286/1 = 286.The minimum required number of clusters is computed by multiplying the effective sample size and ICC factors for both groups [28]. We received the typical value of ICC factor of 0.01 from range values (0.01 to 0.05) based on the existing recommendation [26]. Consequently, the minimum needed cluster number is 329*0.01 = 3.29 for both groups. Nevertheless, to maintain the sufficiency of the cluster and to have adequate power [26, 28], 12 clusters (*12 kebeles*) will be included in this study. To account for the effect of the cluster, the effective sample size is multiplied by a VIF of 1.26. The VIF is calculated with the assumption of an equal cluster size of 27 study subjects from 12 clusters (*kebeles*). Using ICC value of 0.01, (VIF = 1+ [(n-1) ICC]), where ‘n’ is the average cluster size [28]. Thus, the final estimated sample size is 360 (180 in the intervention arm and 180 in the control arm). However, the sample size calculated for the fourth objective which is designed to evaluate the effect of the intervention on MHSU is 1,126 (i.e., larger). Hence, the sample size of 1,126 obtained from the fourth objective will be utilized for this objective as well as it would be maximum or representatives of the sample for both objectives.

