**The measurements**

**ANC utilization** is measured as a proportion of women who utilized ANC from skilled providers (HEWs, midwives, nurses, health officers, and doctors) at least once during the last pregnancy using a woman's self-report. However, different studies considered different figures of ANC visits being optimum. For instance, some researchers had fixed 2 ANC visits to be adequate. The WHO suggests at least 8 ANC visits throughout pregnancy while the first visit will be conducted before 16 weeks or within the first trimester. Therefore, standardization of the numbers of ANC use is required to assist the comparison of diverse or different studies. Accordingly, we considered utilization of ANC as a woman who has at least one ANC follow-up which is similar to EDHS. Besides, the time must be within the first trimester or before 16 weeks of gestation. Moreover, women must consume more than 90 iron-folic acids (IFA) tablets or syrup, receive at least one dose of tetanus toxoid injection, have a laboratory test result of syphilis, and blood group.

**Institutional delivery utilization** is measured as the proportion of women who utilized institutions (governmental health centers or hospitals, and/or private hospitals or clinics) for delivery in their last pregnancy using a woman’s self-report.

**PNC utilization** is measured as the proportion of women who utilized a PNC visit within 42 days after giving birth at least once using a woman’s self-report.

**Maternal knowledge regarding ODS** will be measured using the 30 questions during three phases namely antepartum (9 questions), intrapartum (12 questions), and postpartum (9 questions). The correct answers are assigned a score of 1, while incorrect answers are assigned a score of 0. Lastly, the total knowledge scores range from 0 to 30. The study respondents who spontaneously mention at least 3 ODS during each phase are classified as having “good knowledge” and those who are not able to spontaneously mention 2 or fewer ODS have “poor knowledge”.

**Spontaneous knowledge** is defined as the knowledge of study participants who can name or call an ODS without being read the name of that sign by data collectors. Merely true ODS spontaneously mentioned by study participants will be recorded during the interview.

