**Statistical data analysis**

Data will be entered into Epidata version 3.1 and exported to the Statistical Package for Social Science (SPSS) version 25 and Stata version 14 for further processing and analysis. During the analysis, all quantitative variables will be handled by recoding, calculations, and categorizations before carrying out the main analysis. Descriptive analyses will be carried out to get descriptive measures for the important variables of interest. The descriptive statistic techniques will be utilized for the data organization and presentation. All continuous data will be checked for the normal distribution. If approximately normal distributed the mean and SD will be reported. The missing data will be handled by using multiple imputation methods. The Principal Component Analysis (PCA) will be carried out for the computation of the wealth index. The effect of clustering will be checked by using an Intra-Cluster Correlation Coefficient (ICC) value. The multilevel analysis will be considered if the calculated value of ICC is greater than 5%. Before conducting a multilevel analysis, we will decide whether or not the multilevel model is required by doing a random intercept model. This model offers data regarding ICC which is utilized to determine whether a multilevel model is required or not. If the chi-square test is significant or the ICC value is greater than 5%, the multilevel analysis model is mandatory to consider. Both bi-variable and multivariable analyses using generalized mixed models with random effects will be carried out. The Generalized Estimated Equations (GEE) or multilevel regression models will be utilized to adjust for between and within-cluster variation for adjusted analysis. Those variables with p-values < 0.25 on the bi-variable analysis model will be included in a multivariable regression model to find out predictors independently associated with MHSU adjusting for other variables in the model. The candidate variables will be entered into the multivariable regression model using the ENTER regression method. The basic assumptions of generalized mixed models will be tested before proceeding with the analysis. The stratified and multivariable analyses will be used to control for the potential confounding variables. Effect modification will be examined using stratification and entering effect modifiers into the multivariable analysis model one at a moment. Multicollinearity among the independent variables will be also evaluated using a multiple linear regression model. The variance inflation factor (VIF) < 10 and tolerance statistics > 0.1 will be used to declare the absence of multicollinearity. The presence and strength of a statistically significant association between MHSU and the independent variables will be assessed using adjusted odds ratios (AORs) with a 95% CI. A statistically significant association between the variables of interest will be confirmed when the 95% CI of the AORs did not contain 1. All analyses of the study will be carried out using a 95% CI or 5% level of significance. Though, a statistical significance level will be adjusted to account for the effect of multiple comparisons problem using the Bonferroni corrections methods. The adjusted level of significance is computed by dividing the preset level of significance by the number of statistical tests conducted (outcome variables). In our case, the adjusted level of significance is 0.05/3 = 0.017. Thus, a statistically significant association will be declared when p-value less than 0.017. After the finish of the qualitative data collection, the tape-recorded data will be transcribed verbatim of the local language and translated to English. The coding and analysis of the qualitative data will be done using the thematic content analysis technique by Atlas-Ti software and presented in narratives. A paired t-test will be utilized to measure the mean change from baseline for both groups (intervention and control) groups. Then, an independent t-test will be utilized to compare the mean change of women’s knowledge regarding ODS and BPCR practice scores and MHSU for interventional groups against the mean change of the control group as effect size. To assess the effect of HEI on maternal knowledge regarding ODS and BPCR practice scores and MHSU, an intention-to-treat analysis will be done to compare outcomes between the two groups.

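### The trial is sized at a 5% level but tested at 0.017, a 95% CI rule for significance is left standing beside it, and the divisor of three depends on an MHSU endpoint that is not defined

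*Protocol*

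**What the plan says.** **Sizing.** The Sample size calculation section introduces the trial figures with "The minimum required sample size for the third and fourth objectives is calculated based on the following considerations" and sets "95% CI, and 80% power". The worked example is knowledge of obstetric danger signs (ODS): "P1 = 45.7% (proportion of women’s knowledge regarding ODS during pregnancy) in the control group" and "P2= 62.9% (proportion of women’s knowledge regarding ODS during pregnancy in the intervention arm". It gives 286 women, multiplied by 1.26 to 360. The adopted size of 1,126 comes from the MHSU objective. Its rates, effect and intracluster correlation (ICC) are not given.

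**Testing.** The Statistical data analysis section contains, in this order:
- "A statistically significant association between the variables of interest will be confirmed when the 95% CI of the AORs did not contain 1";
- a general 5% level for all analyses;
- a Bonferroni adjustment in which the divisor is the number of tests, equated with outcome variables: "In our case, the adjusted level of significance is 0.05/3 = 0.017";
- a closing rule that significance is declared below 0.017.

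**Outcomes.** Research hypothesis and The study variables name three quantitative outcomes: ODS knowledge, birth preparedness and complication readiness (BPCR) practice, and MHSU. The measurements section gives utilization as three separate proportions, for antenatal care (ANC), institutional delivery and postnatal care (PNC). The last, for example, "is measured as the proportion of women who utilized a PNC visit within 42 days after giving birth at least once". No composite or score joins them.

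**The concern.** Three parts of one decision procedure do not fit together.

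- The level used to choose the sample size is not the level used to judge the result, so the stated power does not describe the planned test.
- Two thresholds for significance sit in the same section. For an MHSU odds ratio with p between 0.017 and 0.05, the conclusion depends on which sentence is cited.
- The correction divides by three, but the definitions supply no single MHSU variable to be the third test.

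These sentences decide whether the trial is reported as positive. The Blinding section says that neither the research team nor the respondents are masked, which is a further reason to settle the rule and the endpoint beforehand.

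**Working it through.** **1. Reproduce the plan's figure, to see which level was used.** Inputs from Sample size calculation: p1 = 0.457, p2 = 0.629, difference d = 0.172, mean p = 0.543, power 80%.

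n per arm = [z_α·√(2·p̄·q̄) + z_β·√(p1q1 + p2q2)]² / d²

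- Two-sided 5%: [1.960 × 0.7045 + 0.842 × 0.6939]² / 0.02958 = 130.5, so 131 per arm (262 in total).
- With continuity correction, (n/4)·[1 + √(1 + 4/(n·d))]² = 141.9, so 142 per arm, **284 in total against the stated 286**.
- One-sided 5% gives 206, or 228 with continuity correction, so it does not fit.
- Inflation: 1 + 26 × 0.01 = 1.26, and 286 × 1.26 = 360, as stated.
- The same inputs at 0.017 (z = 2.387) with continuity correction need 185 per arm, 370 in total, and 370 × 1.26 ≈ 467.

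The displayed sizing is therefore two-sided 5% without adjustment.

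**2. Power at the tested level for the outcome that set 1,126 (MHSU).** Assumption: 1,126 gives exactly 80% power at two-sided 5%.

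- Standardised effect: 1.960 + 0.842 = 2.802.
- At 0.017: Φ(2.802 − 2.387) = Φ(0.415) ≈ **66%**.
- At 0.01 (five tests): Φ(2.802 − 2.576) = Φ(0.226) ≈ **59%**.

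**3. Power for ODS knowledge at the adopted size.** 1,126 women in 12 kebeles give a mean cluster size of 93.8. The design effect is 1 + 92.8 × ICC, and the effective n per arm is 563 divided by it. The ICC values span the protocol's quoted range of 0.01 to 0.05. The power formula is the normal approximation for two proportions, without continuity correction.

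| ICC | Design effect | Effective n per arm | Power at 0.05 | Power at 0.017 |
|---|---|---|---|---|
| 0.01 (protocol's choice) | 1.93 | 292 | 98.8% | 96.5% |
| 0.02 | 2.86 | 197 | 93.2% | 85.5% |
| 0.03 | 3.78 | 149 | 84.9% | 72.6% |
| 0.05 | 5.64 | 100 | 68.7% | 52.1% |

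**4. The two rules.** A 95% CI for an AOR that excludes 1 corresponds to p < 0.05. The interval corresponding to p < 0.017 is the 98.3% CI (1 − 0.017). Every MHSU result with 0.017 ≤ p < 0.05 is classified differently by the two.

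**5. The divisor.**

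- MHSU as one endpoint: three tests, 3 × 0.017 = 0.051, which is the intended 5% apart from rounding.
- ANC, delivery and PNC tested separately, plus knowledge and BPCR: five tests. The bound is 5 × 0.017 = **8.5%**; if independent, 1 − 0.983⁵ = **8.2%**. The Bonferroni level would be 0.05/5 = 0.01.

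**The case against.** **The text resolves itself.** The 5% level can be read as a default, followed by an explicit override to 0.017, and the 95% CI sentence sits in the text on predictors of MHSU. Much of this stands: the final p-value rule is clear, and the CI sentence fits the cross-sectional analysis. But that sentence is not confined to it, the 0.017 rule also speaks of associations, and nothing withdraws the 95% interval. The conflict remains for MHSU odds ratios.

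**Three is the protocol's own count.** This is correct. The hypothesis and the outcome table both list three quantitative outcomes, and the planned comparison of mean change in MHSU suggests one measure. A reader might infer that the protocol defines five outcomes; it does not. Five arises only if MHSU is tested through its three measures. What stands is that the count is unresolved.

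**Power is not shown to be short.** This stands in part. A reader might infer that the whole trial is underpowered, but at the protocol's ICC the knowledge outcome keeps 96.5% at 0.017. For MHSU the 66% is conditional, because the inputs to 1,126 are absent.

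**Two further inferences are not supported.**

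- One is a family-wise error of 22.6% (1 − 0.95⁵) from applying the 95% CI rule to five tests. Knowledge and BPCR scores are analysed by linear models and t-tests, which yield no odds ratio. At most the three MHSU measures could fall under that rule: 1 − 0.95³ = 14.3% if independent.
- The other is that about 1,500 women are needed, since ((2.387 + 0.842)/2.802)² = 1.33 and 1,126 × 1.33 ≈ 1,500. That ratio applies to effective size, so it holds only if kebeles are added in proportion. With 12 kebeles and ICC 0.01 (assumed for MHSU), the effective total is 1,126/1.928 = 584. Solving N/[1 + (N/12 − 1) × 0.01] = 584 × 1.328 gives about 2,170. Neither figure is a basis for changing the size while the MHSU inputs are unknown.

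**Conclusion.** The concern holds in three limited parts.

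- **Level.** The displayed sizing uses two-sided 5%, while significance requires p < 0.017. This is certain for the worked example. For MHSU it follows from the considerations being stated for both trial objectives, but the 1,126 cannot be reproduced. The fall from 80% to about 66% rests on the assumption that 1,126 was sized at exactly 80% and 5%. For knowledge the consequence is small at ICC 0.01 and grows with the ICC.
- **Rule.** For MHSU odds ratios, p between 0.017 and 0.05 leads to opposite conclusions under two sentences of the same section.
- **Count.** Dividing by three controls the error only if MHSU is a single endpoint. If its three measures are tested separately, family-wise error is up to 8.5% instead of 5%.

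The document does not show that the trial as a whole is underpowered, or that it must enrol more women.

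**What to change.** 1. For the trial outcomes, make the adjusted p-value the only decision rule and report matching intervals: 98.3% for three tests, 99% for five. Limit the 95% CI rule expressly to the cross-sectional predictor analysis.
2. Either define MHSU as one endpoint, stating how ANC, institutional delivery and PNC are combined, or count the three measures separately and divide by five (0.01).
3. Show the rates, effect, ICC and level behind 1,126, and restate its power at the level that will be tested. Take the figure from those inputs; the 66% here is conditional and should not be copied into the protocol.

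Bonferroni is valid and need not be replaced. If a step-down method such as Holm were preferred, fixed 98.3% intervals would no longer match its decisions.

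The cost is wording, one recalculation and probably a less favourable stated power. No additional women are needed.

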**Methods:** A community-based cross-sectional study will be carried out to assess the utilization and predictors of maternal health care. A phenomenological qualitative study will be conducted to explore perceptions, barriers, and facilitators of maternal health care. A cluster randomized controlled trial will be employed to assess the effect of health education on maternal knowledge about the obstetric danger signs, birth preparedness and complication readiness plan, and maternal health service utilization (MHSU). The minimum required sample size is 1,104 for a cross-sectional study. To explore perceptions, barriers, and facilitators of maternal health care a minimum of 20 in-depth interviews, 3 focus group discussions per group, and 20 key informative interviews will be conducted. The minimum required sample size to assess the effect of health education on outcomes is 1,126. A multi-stage sampling method will be used to select the study participants for a cross-sectional study. A maximum variance sampling method will be used for the qualitative study. A cluster-randomized sampling method will be utilized for the interventional study. Quantitative data will be collected using a validated, pre-tested, and structured questionnaire. Qualitative data will be collected using pre-tested focus group discussions, in-depth interviews, and key informant interviews guides until information saturation is reached. The intervention group will be received 12 rounds of pre-recorded audio-based health education. The utilization of maternal health care will be measured at baseline and 6 months after the intervention. Data will be entered into Epi Data version 3.1 and exported to the SPSS and Stata software for analysis. Descriptive analyses will be carried out to get descriptive measures for the important variables of interest. The generalized estimated equations analysis will be used to assess the potential predictors of MHSU. The coding and analysis of the qualitative data will be done using the thematic content analysis technique by Atlas-Ti software and presented in narratives. For maternal knowledge about the danger signs and practice of birth preparedness and complication readiness, the multilevel linear regression models will be utilized. The intention-to-treat analysis will be used to compare outcomes between groups. Paired and independent t-tests will be used to compare the effect of an intervention. Statistical significance level will be adjusted to account for the effect of multiple comparisons problems using the Bonferroni corrections methods.

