**The study variables**

| Outcome variables | Definition |
| --- | --- |
| MHSU | Utilization of maternal health care measured using the yes or no questions at the baseline and after 6 months of intervention. |
| Knowledge of obstetrics danger signs | Will be measured by using the 30 knowledge assessment questions. |
| Birth preparedness and complication readiness practice | Will be assessed using the 5 practice assessment questions. |
| Perceptions, barriers, and facilitators | Perceptions, barriers, and facilitators of MHSU that affect the utilization of MHS will be explored qualitatively. |
| Exposure variable | Definition |
| Health education | **Intervention group:** will receive routine plus pre-recorded audio-based HEI package for six months until date of delivery.  **Comparator group:** will receive the routine health education package for six months until the date of delivery as per the Ethiopian guidelines. |
| Predictors | Predictors that predict the utilization of MHS. It will be measured retrospectively. Socio-economic and demographic, obstetric characteristics, health facility and socio-cultural related predictors. |
| Covariates | Place of residence (urban/rural), educational status of women and her spouse, wealth index, maternal age, occupational status of women and her spouse |

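### The effect on the knowledge and BPCR scores is fixed as change against change with no baseline score in any model, which usually costs precision and over-corrects chance imbalance between 12 kebeles

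*Protocol*

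**What the plan says.** The Statistical data analysis section sets out two steps for the knowledge and BPCR scores. First, "A paired t-test will be utilized to measure the mean change from baseline for both groups". Second, an independent t-test compares the intervention arm's mean change "against the mean change of the control group as effect size". The Summary repeats this: "Paired and independent t-tests will be used to compare the effect of an intervention".

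Regression models are also named. For the two scores, the Summary says that "the multilevel linear regression models will be utilized". The analysis section adds that GEE or multilevel models "will be utilized to adjust for between and within-cluster variation for adjusted analysis". Neither place mentions a baseline score as a model term.

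The covariates row in The study variables reads "Place of residence (urban/rural), educational status of women and her spouse, wealth index, maternal age, occupational status of women and her spouse". It holds no baseline outcome.

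Both outcomes exist as scores. For knowledge, The measurements says that "the total knowledge scores range from 0 to 30". For BPCR, The study variables says "Will be assessed using the 5 practice assessment questions".

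**The concern.** Subtracting baseline is the same as adjusting for it with the slope fixed at 1. Two recall-based scores taken six months apart are unlikely to be that closely related. When the true slope is lower, two things follow.

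- **Precision.** Baseline noise is carried into the comparison in full, so the standard error is larger than it need be.
- **Imbalance.** Suppose one arm starts lower by chance, as can easily happen with 12 kebeles. Part of that gap closes by regression to the mean, and the change score counts the closing as an effect.

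At stake is the precision of the Paper III comparisons and how they read if the arms differ at baseline. The trial must collect baseline scores anyway to compute change.

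**Working it through.** **1. The plan's own figures.** Inputs from Sample size calculation: 45.7% against 62.9%, 95% confidence, 80% power. The two-proportion formula with continuity correction gives 142 per arm, 284 in total, against the stated 286. The inflation factor is 1 + 26 × 0.01 = 1.26, and 286 × 1.26 = 360.4, against the stated 360. These figures reproduce, so the point does not rest on an arithmetic error. The number used is 1,126, or 1,126/12 ≈ 94 women per kebele.

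**2. Variance with a single correlation.** Let rho be the baseline to 6-month correlation, with equal SDs at both times. The arm-difference variance is proportional to 2(1 − rho) for change and 1 − rho² for the baseline-adjusted score. The ratio of change to adjusted is 2/(1 + rho):

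- rho 0.3: 1.40/0.91 = 1.54, SE 24% larger
- rho 0.5: 1.00/0.75 = 1.33, SE 15% larger
- rho 0.7: 0.60/0.51 = 1.18, SE 8% larger

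**3. The same in a cluster analysis.** Assume six kebeles per arm, 94 women each, kebele-level correlation c and scores in SD units. Let V = ICC + (1 − ICC)/94 and C = ICC·c + (1 − ICC)·rho/94. The arm-difference variances are:

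- change: 2(V − C)/3
- own baseline only, slope rho: [V(1 + rho²) − 2·rho·C]/3
- own plus kebele-mean baseline: 1.125 × (V − C²/V)/3, where 1.125 = 1 + 1/8 is the average cost of estimating the kebele-level slope from 12 kebeles

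| ICC | rho | c | SE change | SE own baseline | SE own + kebele mean |
|---|---|---|---|---|---|
| 0.01 | 0.3 | 0.3 | 0.098 | 0.079 | 0.084 |
| 0.01 | 0.5 | 0.5 | 0.083 | 0.072 | 0.076 |
| 0.01 | 0.7 | 0.7 | 0.064 | 0.059 | 0.063 |
| 0.01 | 0.3 | 0.8 | 0.079 | 0.072 | 0.074 |
| 0.05 | 0.3 | 0.8 | 0.107 | 0.115 | 0.105 |

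Worked last row: V = 0.05 + 0.95/94 = 0.0601; C = 0.040 + 0.0030 = 0.0430. Change: 2 × 0.0171/3 = 0.0114. Own baseline: (0.0655 − 0.0258)/3 = 0.0132. With the kebele mean: 1.125 × 0.0293/3 = 0.0110. Simulation of the same row gave SEs of 0.109, 0.114 and 0.106. For the first row it gave 0.097 to 0.098 for change and 0.079 for own baseline.

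The protocol's planning ICC is 0.01, from a quoted range of 0.01 to 0.05.

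**4. Imbalance.** When c = rho, the change-score estimate moves by −(1 − rho) per unit of baseline difference: −0.7, −0.5 and −0.3. The adjusted estimate moves by about 0. At ICC 0.01 the SE of the baseline difference is √(V/3) = √(0.0205/3) = 0.083 SD. A one-SE imbalance at rho 0.3 therefore shifts the change-score estimate by 0.7 × 0.083 = 0.058 SD. In the last row of the table the shift is C/V − 1 = −0.28 for change, but C/V − 0.3 = +0.42 for own baseline alone.

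**5. Power at the protocol's 0.017 threshold.** ICC 0.01, rho = c = 0.3; t test with 10 df (9 with the kebele mean).

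| Effect | Change | Own baseline | Own + kebele mean |
|---|---|---|---|
| 0.27 SD (assumed, not in the protocol) | 49% | 70% | 62% |
| 0.44 SD (45.7% vs 62.9% on a probit scale) | 92% | 99% | about 97.5% |

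**The case against.** Four things can fairly be said for the plan.

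- **The change score is valid.** It is unbiased over randomisation. A reader might infer that the comparison is biased or invalid because it uses change scores. It is not; the over-correction is conditional on an imbalance having occurred. This stands.
- **Adjustment is not always better.** A reader might infer that adjustment wins at every rho and however clustering is handled, or that below rho 0.5 subtracting baseline is always worse than ignoring it. Both hold when kebele-level and individual correlations are equal, but not in general. In the last row of the table, own-score adjustment loses to change (0.115 against 0.107). There the change score also beats ignoring baseline, whose SE is √(0.0601/3) = 0.142. This stands, and it shapes the fix.
- **Power is ample under the plan's assumptions.** Objective 3 needs 360 women and 1,126 are planned. A reader might infer that Paper III is underpowered. At the planning effect the documents do not support that. The larger gap appears only at an assumed smaller effect.
- **Model terms may be left to an SAP.** The covariates row is not said to be exhaustive, and the multilevel models could yet include baseline. This stands for the covariate list. It does not reach the analysis section, which positively names change against change as the effect.

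Separately, a t-test on individual women ignores clustering. That is a different fault. The comparison above uses a cluster-level analysis throughout, so it does not depend on it.

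**Conclusion.** The point holds as an improvement in efficiency and in handling chance imbalance. The protocol commits to a change-score effect and nowhere adjusts for the baseline it collects.

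With equal correlations at both levels, the variance penalty is about 54%, 33% and 18% at rho 0.3, 0.5 and 0.7. Rho is assumed, since the protocol gives none. At ICC 0.01 and rho 0.3 the penalty shrinks when kebele means are stable over time: the own-baseline to change variance ratio goes from 0.65 at c = 0.3 to 0.0157/0.0187 = 0.84 at c = 0.8. It reverses at ICC 0.05 with c = 0.8 and rho 0.3 unless the kebele-mean baseline is added.

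That extra term is insurance and has a price. With equal correlations the SE gain over change falls to almost nothing at rho 0.7 (0.063 against 0.064).

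At the 0.017 threshold and the planning effect (about 0.44 SD, itself a conversion), power at rho 0.3 is above 90% either way. The practical weight is therefore moderate: narrower intervals and an estimate less sensitive to where the arms start.

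**What to change.** In Statistical data analysis, define the effect for the knowledge and BPCR scores as the arm difference in the 6-month score, estimated from the multilevel linear model that the Summary already names. Specify in the model:

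- a kebele random effect, kept whatever the ICC screen in that section shows;
- small-cluster degrees of freedom, about 12 − 2 − 1 = 9;
- the woman's own baseline score and the kebele-mean baseline score as covariates;
- the stated 0.017 threshold for the comparison.

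Add both baseline terms to the covariates row in The study variables. Keep change from baseline, including the paired comparisons, as description only, and align the Summary.

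The cost is one or two model terms, one kebele-level degree of freedom and a few sentences of text. No new data are needed. Fixing this before outcomes are compared also removes a later choice between change, 6-month-only and adjusted estimates.
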